### **13. Medical ethics requirements and protection of subjects' rights and interests**

This clinical trial will follow the Helsinki Declaration (Fortaleza, Brazil, the 64th World Medical Association Joint Conference, 2013) and relevant drug clinical trials research norms and regulations in China. The clinical trial plan must be approved by the Medical Ethics Committee of the responsible research institution before implementation. The investigator must provide the subject with detailed information about the clinical trial and sign the patient's informed consent prior to the trial. If clinical trial need to modify the original plan, they must be reported to the Medical Ethics Committee and approved before implementation. Subjects can receive timely medical treatment when adverse reactions occur during the trial.

### **14. Subject's medication compliance**

In this clinical trial, attention should be paid to the subject's compliance with the use of medication. Patients should be fully aware of the importance of on-time medication and strictly follow the prescribed medication. The reasons for not using the prescribed drugs should be recorded in detail.

## **15. Data management and statistical analysis**

### **15.1 Monitoring of Data Records**

The leader of the responsible institution shall periodically visit each trial center to check the subject's informed consent and screening situation during the trial process, as well as confirm that all eCRFs are filled in correctly and consistent with the original data. Besides, the investigator shall also confirm that all errors or omissions have been corrected or indicated and then signed and dated. Furthermore, the situation of each subject's dose change, treatment change, combined medications, intercurrent illness, loss of follow-up, examination omissions, etc. should be exactly confirmed and recorded and the verification of the subject's withdrawal must be described in the eCRF.

The leader shall also confirm that all adverse events have been recorded and especially serious adverse events have been recorded and reported within the specified time. What's more, the leader should verify whether the trial drug has been supplied, stored, distributed, and withdrawn in accordance with relevant regulations and records has been made accordingly.

When verifying the original medical records, it should be noted that the records should be timely, accurate, truthful, standardized, and complete. In particular: (1) Whether the eligible subjects meet the inclusion and exclusion criteria; (2) Whether the names, dosages, and usages of the trial drugs are recorded on the original medical records and whether the prohibited drugs prescribed in the clinical trial program are used; (3) Whether the original medical record observation, examination items and records are consistent with the eCRF. (4) Whether the degree of severity of illness, efficacy determination and safety evaluation are correct. (5) Whether the name, address, telephone number, medical record number and admission number of the subject is filled in exactly. (6) Carefully record the patient's medication situation, make detailed records of the patient's compliance, and especially make a detailed record of the situation of all use, sometimes use, and half of the unused. (7) Data within the normal range should be recorded, while data that is significantly higher or outside the clinically acceptable range should be verified and recoded by the physician participating in the clinical trial. (8) Clinical observation forms should always be recorded using a pen. Each page needs to be signed and dated.

### **15.2 Data entry and modification**

EDC software is used to compile data entry procedures for data entry and management by data administrators which jointly designated by the sponsor and the statistical organizations. In order to ensure the accuracy of the data, two data entry staff should be independently entered twice and compared.

### Multi-center, Randomized, Double-blind, Controlled Study of the Effectiveness and Safety of Mifepristone in Treating Adenomyosis

For questions in the electronic case report form, the data administrator will generate a question answering form and issue an inquiry to the researcher through the clinical monitor. The researcher should answer and return as soon as possible. The data administrator will modify, confirm and entry the data according to the researcher's answer. If necessary, the data administrator can re-generate a question answering form.

## 15.3 Data locking

When all electronic case report forms (eCRF) are entered into the EDC database in duplicate, and after questioning and verification, the sponsors and statisticians lock the data. Hence, the locked data files cannot be modified anymore.

## 15.4 Selection of statistical analysis data

Full Analysis Set (FAS): According to the basic principles of intentionality analysis (ITT), statistical analysis is performed on all randomized cases and patients without any valid data at baselined will be excluded. For the uncompleted clinical trial observations data, last-observation-carry-forward is conducted at the end of the trial. The number of subjects whose efficacy will be evaluated at endpoint is the same as at the beginning of the trial. Per Protocol Set (PPS): All data from those well compliant subjects (taking 80% to 120% of the applied trial drug dose), which compliant with the protocol and have not taking the prohibited drug during the trial, as well as have VAS assessed at baseline, and have at least one follow-up VAS record. Safety Set (SS): All subjects who were randomized and have taken at least once clinical trial drug and have at least once safety evaluation should be evaluated for safety.

## 15.5 Statistical analysis method

### (1) General principles

SAS is used for statistical analysis.

Two-sided tests are used in all statistical tests with an Alpha level of 0.05.

The mean, standard deviation, median, minimum, maximum, and interquartile range will be calculated in the description of quantitative indicators.

Various types of cases and percentages are used in the description of the classification index.

### (2) Case characteristics

Enrollment and completion: Summarize the number of cases enrolled and completed by each center, and list the unfinished cases and cases that do not enter each population.

Multi-center, Randomized, Double-blind, Controlled Study of the Effectiveness and Safety of  
Mifepristone in Treating Adenomyosis

(3) General information and baseline characteristics

The baseline is defined as Interview 1 (Day 0-3), and the SS is evaluated at baseline.

Baseline descriptions are made on the age, sex, allergy history, medication history, history of illness, and laboratory tests for each group of population.

(4) Analysis of safety indicators

The SS population is used for analysis.

Describe the number of occurrences of adverse events and adverse reactions of the total and each group and give the corresponding list in the detailed account.

Compared with the laboratory tests before the treatment, the situations after the treatment of each interview are described in the form of the crosstabs, and the abnormalities that are significant after the treatment are listed.

The vital signs indicators of each interview relative to the baseline during interviews and after treatment are described, and t-test or non-parametric test is used for intragroup comparison.

(5) Analysis of efficacy indicators

FAS and PP populations are used for analysis.

Baseline: Baseline description of each efficacy indicator.

**Primary effectiveness variable**

The primary effectiveness variable is assessment of adenomyosis-associated pain by VAS at week 12 (at the end of the double-blind portion) and compared with baseline period (interview 2). Using the covariance analysis (ANCOVA), baseline VAS scores are used as covariates to compare the differences in the VAS scores at the 12th week. At the same time, comparisons were made during each interview (interview 2-5). For the missing data, the method of Last Observation Carried Forward (LOCF) will be used. Further details of the method can be found in the statistical analysis plan.

**Secondary effectiveness variable**

Pictorial blood loss assessment chart (PBAC), uterine volume and hemoglobin changes, and safety (e.g., adverse events, vaginal bleeding, gynecological safety).

The detailed analysis of secondary effectiveness variable is seen in the statistical analysis plan.

**Safety variable**

Descriptive analysis of safety variables will be performed. The relative change in BMD (expressed as a percentage) at 12 weeks and at the end of treatment compared to baseline will be presented as descriptive statistics. In addition, 95% confidence intervals will be provided for each treatment

Multi-center, Randomized, Double-blind, Controlled Study of the Effectiveness and Safety of Mifepristone in Treating Adenomyosis group.

#### (1) Medication compliance

Medication compliance is described by measurement data.

Compliance is segmented by <80%, 80-120%, and >120%, and is described by ranked data.

#### **Determination of sample size**

In correlational studies, mifepristone treatment of adenomyosis reduced the VAS score from  $8.49 \pm 1.83$  before treatment to  $2.01 \pm 0.87$ . The average value before and after treatment decreased by 6.48. Although there are many related literatures about placebo, they are quite different. Based on the principle of conservation, we make the following assumptions:

- The VAS score after 12 weeks of treatment in the mifepristone group was approximately 2.01;
- The VAS score after 12 weeks of treatment in the placebo group was approximately 3.25;
- The standard deviation of VAS scores between two groups after treatment was similar (about 2.31).

Using a margin of error of  $\alpha=0.05$  and a potency of 0.9 ( $\beta=0.1$ ) in a two-sided test, 60 subjects need to be evaluated in each treatment group, which can demonstrate that mifepristone is superior to placebo. After considering loss of follow-up, violations of research protocols, compliance and other factors, each group needs to add 25% of the subjects, thereby ensuring that at least 60 subjects in each group complete the study. Therefore, at least 75 subjects should be selected for each treatment group.

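### The stated 60 evaluable subjects per group give 83% power, not 90%, on the protocol's own inputs; 60 is what a one-sided 0.05 test would need

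*Protocol*

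**What the plan says.** Everything needed for the calculation is in the protocol, section 15.5, under Determination of sample size.

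- Mifepristone mean: "The VAS score after 12 weeks of treatment in the mifepristone group was approximately 2.01".
- Placebo mean: "The VAS score after 12 weeks of treatment in the placebo group was approximately 3.25".
- Spread: "The standard deviation of VAS scores between two groups after treatment was similar (about 2.31").
- Error rates: alpha 0.05 and a "potency of 0.9".
- Result: "in a two-sided test, 60 subjects need to be evaluated in each treatment group, which can demonstrate that mifepristone is superior to placebo".

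The section then adds 25% to each group for losses, protocol violations and poor compliance, "thereby ensuring that at least 60 subjects in each group complete the study". This gives 75 per group, 150 in total.

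The sidedness is not in doubt. Section 15.5 (1), General principles, states: "Two-sided tests are used in all statistical tests with an Alpha level of 0.05".

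**The concern.** A difference of 1.24 with an SD of 2.31 is a standardised effect of 0.537. For 90% power in a two-sided 0.05 test, 60 per group is visibly too few for an effect of that size.

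This calculation is the only justification the protocol gives for its 150 subjects. If it is wrong, ethics committees and readers are told that the planned number of completers carries a 10% risk of missing the assumed effect when the real risk is higher. A null result would then be read against an overstated power.

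**Working it through.** **Inputs**, all from Determination of sample size: difference 3.25 − 2.01 = 1.24; common SD 2.31; 1:1 allocation; two-sided alpha 0.05; power 0.90.

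**Formula** (normal approximation, per group): n = 2 × (z_alpha + z_power)² × (SD / difference)², where (2.31 / 1.24)² = 3.470.

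**1. Reproducing the protocol's 60.** With the one-sided quantile:

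n = 2 × (1.645 + 1.282)² × 3.470 = 59.4, rounded up to 60.

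This matches the stated figure and changes nothing but the sidedness.

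**2. As the protocol specifies, two-sided:**

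n = 2 × (1.960 + 1.282)² × 3.470 = 72.9, rounded up to 73.

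The exact noncentral t calculation gives 74.

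**3. Power** (exact t test, noncentrality = 1.24 / (2.31 × √(2/n)), which is 2.94 at n = 60):

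| Evaluable per group | Two-sided power | One-sided power |
|---|---|---|
| 60 | 83.1% | 89.9% |
| 73 | 89.6% | 94.3% |
| 74 | 90.0% | 94.6% |
| 75 | 90.4% | 94.8% |

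The normal approximation gives 83.7% two-sided at 60. The choice between normal and t therefore moves the answer by less than one point and cannot explain a shortfall of 13 to 14 subjects per group. The type II error at 60 is 16.9%, about 1.7 times the stated 10%.

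**4. What would make 60 correct in a two-sided test.** One of the following would have to hold, and the protocol states none of them:

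- a difference of about 1.38 instead of 1.24;
- an SD of about 2.08 instead of 2.31 (2.31 × 1.24 / 1.38);
- a baseline to week-12 correlation of about 0.44 exploited by the ANCOVA, which multiplies the residual variance by 1 − r².

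**5. The loss allowance.** 60 × 1.25 = 75. Since 74 evaluable subjects are needed for 90%, the margin is 75 − 74 = 1 per group, not 15. Had the same 25% been added to the correct figure, the target would have been 73 × 1.25 = 91.25 to 74 × 1.25 = 92.5, that is 92 to 93 per group.

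**The case against.** Four points can be made for the protocol as written.

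**Carried-forward values keep subjects in the analysis.** Section 15.4 retains randomised subjects in the full analysis set with last observation carried forward, so close to 75 per group may enter the primary analysis, and 75 gives 90.4%. This is fair, and it means that 83% describes the planned completer number rather than necessarily the full analysis set. It does not repair the statement, because the protocol ties its 90% to 60 evaluable subjects. Nor does it secure 90% in practice: retained subjects help in full only if their carried values hold the whole 1.24. No dilution figure is given, so as assumptions at 75 per group:

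| Assumed dilution of the 1.24 | Power |
|---|---|
| 5% | 87% |
| 10% | 84% |
| 20% | 74% |

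The last row is severe: if 15 of 75 are lost, it corresponds to their carried values showing no treatment effect at all.

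**ANCOVA is more precise than a comparison of means.** This is true, and it could restore 90% at 60 if the correlation were about 0.44 or higher. At assumed correlations of 0.3 and 0.4, power at 60 is 86.4% and 88.9%. The protocol states no correlation, and its SD is described as that of post-treatment scores, which reads as unadjusted.

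**The SD may be pessimistic.** The section quotes a post-treatment SD of 0.87 on mifepristone from earlier work. With 0.87 in one arm and 2.31 in the other, power at 60 would be about 97%. The protocol nevertheless chose 2.31 for both arms, as a conservative assumption, and its stated power must follow from that choice.

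**The one-sided explanation is an inference.** This stands. A two-sided calculation with SDs of 1.83 and 2.31 also gives 59.4, but 1.83 is a pre-treatment SD and this route contradicts the assumption of similar SDs. The discrepancy exists whatever its origin.

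**Conclusion.** The concern holds. On the protocol's own assumptions (difference 1.24, common SD 2.31, two-sided 0.05, no covariate gain), 60 evaluable subjects per group give 83% power, and 90% needs 74. Among calculations that keep every other stated input, the one-sided version is the one that returns 60.

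The error lies in the stated power and in the loss allowance built on it. It does not affect the type I error or the planned analysis. How far the primary analysis itself falls short depends on how many subjects it retains and how much effect their carried-forward values hold: from 90.4% with all 75 per group and no dilution, downwards. The figures change if the true SD is smaller or if baseline adjustment gains precision, but the protocol claims neither as the basis for 60.

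**What to change.** Correct the sentence in Determination of sample size, for example:

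> With 60 evaluable subjects per group, a two-sided alpha of 0.05, a difference of 1.24 and an SD of 2.31, the power is 83%; 90% power would require 74 evaluable subjects per group.

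Add that 75 per group gives 90.4% only if all are evaluable and the assumed difference is undiluted.

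The calculation could instead be based on the planned ANCOVA, but only if a baseline to week-12 correlation is stated with its source. A value of about 0.44 adopted because it returns 60 would be back-fitting.

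The cost is wording in the protocol, and in the SAP if it repeats the figure. Enrolment and analysis are unchanged; the stated power becomes less favourable.

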## 15.6 The monitoring system

The person in charge of the sponsor conducts a systematic examination of the clinical trials and monitors the trials in accordance with the GCP principle, in order to ensure that the trial program is conducted in accordance with regulations and that the data recorded in the case reporting forms are the same as the original data.

## 16. The management of clinical trial drug

### 16.1 Trial drug packaging

Each hospital distributes the corresponding numbered drugs, and the research drugs are uniformly stored and managed by the trial institution. Each center screens patients, and the qualified ones are

Multi-center, Randomized, Double-blind, Controlled Study of the Effectiveness and Safety of Mifepristone in Treating Adenomyosis  
selected, and the trial drug distributor distributes the drugs according to the order of the number of trial drugs for each subject (note: those who meet the inclusion criterion may be given the drugs). The trial drug distributor shall promptly fill in the "Trial Drug Management Registration Record" and the remaining drugs shall be recycled and then destroyed. Each package comes with a drug label, which contains the statutory contents such as approval number, drug number, drug name, quantity, major functions, usage, storage conditions, and drug supply institution.

## 16.2 Trial drug distribution

After China Resources Zizhu Pharmaceutical Co., Ltd. uniformly prepares and packages the trial drugs, the trial drugs are distributed according to the required amount to the Women's Hospital, School of Medicine Zhejiang University, and managed by special personnel and distributed to each trial center.

Each trial center is uniformly accepted by special personnel to manage trial drugs and handle the handover procedures.

According to the drug number, the drugs will be sent to the subjects by special personnel according to the number of the subject's visit in the order from the smallest to the largest in each trial center. Each center shall register the clinical release status of the drug, and at the end of the trial, the registration record of trial drugs shall be submitted to the sponsor for examination by the drug regulatory department.

## 16.3 Trial drug inventory

Trial drug supply: The applicant provides trial drugs (certifications for trial drugs) in accordance with the requirements of clinical trials, and the researcher establishes the record cards of clinical trial drug administration to check whether the quantity, quality, and the drug code of the trial drug are correct.

Trial drug distribution: In the process of trial drug distribution, special personnel will check the drug, record the usage, and ensure that the drug is properly dispensed in accordance with the principle of sequence of visits.

Trial drug recovery: After the end of the trial, special personnel will perform recovery and destruction of the remaining trial drugs.

## 16.4 Trial drug preservation

Trial drugs should be uniformly managed and preserved, and be handed out by special personnel. Select appropriate storage locations, ensure scientific storage conditions, and regularly check the quality and storage environment of trial drugs.

## **17. Modification of the program**

After the program is approved by the Ethical Committee, if any changes are made, a "program modification explanation" must be written and signed by the principal researcher, and it must be approved by the ethics committee before implementation. After the program is revised, it must be accepted and signed by the sponsor; anyone who participates in the trial must not violate the program.

## **18. Summary and preservation of data**

### **18.1 Data summary**

After the completion of the clinical trial, the statistical institution will process the data according to the statistical requirements. Each clinical trial participant shall write a clinical trial summary form according to the unified requirements. The clinical trial responsible institution shall summarize the trial summary forms of each trial participant and write a clinical trial summary report. Based on this, an overall assessment of the clinical efficacy and safety of the drug is made.

### **18.2 Data preservation**

Researcher saves all research data, including confirmation of all participants (can effectively check different records, such as hospital records), all original signed informed consent of patients, all study records, electronic case report forms, detailed records of drug distribution, etc. The researchers should keep the clinical trial data for five years after the termination of the clinical trial.

